## Abstract

**Background:**

In bipolar spectrum disorder, some individuals experience ongoing, frequent fluctuations in mood outside of affective episodes. There are currently no evidence-based psychological interventions designed to address this. This feasibility study is a phase II evaluation of a dialectical behavioural therapy-informed approach (Therapy for Inter-episode mood Variability in Bipolar [ThrIVe-B]). It seeks to examine the feasibility and acceptability of a future definitive trial evaluating the clinical and cost effectiveness of the ThrIVe-B programme.

**Methods/design:**

Patients will be randomised 1:1 to either treatment as usual only (control arm) or the ThrIVe-B intervention plus treatment as usual (intervention arm). Follow-up points will be at 3, 6, 9 and 15 months after baseline, with 9 months as the primary end point for the candidate primary outcome measures. We aim to recruit 48 individuals meeting diagnostic criteria for a bipolar spectrum disorder and reporting frequent mood swings outside of acute episodes, through primary and secondary care services and self-referral. To evaluate feasibility and acceptability, we will examine recruitment and retention rates, completion rates for study measures and feedback from participants on their experience of study participation and therapy.

**Discussion:**

Proceeding to a definitive trial will be indicated if the following criteria are met: (1) trial participation does not lead to serious negative consequences for our participants; (2) any serious concerns about the acceptability and feasibility of the trial procedures can be rectified prior to a definitive trial; (3) follow-up data at 9 months are available for at least 60% of participants; (4) at least 60% of patients in the ThrIVe-B arm complete treatment.

**Trial registration:**

ISRCTN, ISRCTN54234300. Registered on 20 July 2017.

**Electronic supplementary material:**

The online version of this article (10.1186/s13063-018-2926-7) contains supplementary material, which is available to authorized users.

## Background

Bipolar disorders (BDs; comprising bipolar II and II disorder and cyclothymic disorder) are associated with considerable personal costs, including increased risk of premature death and of suicide [1]. The societal economic cost is also high: In 2007, BDs cost the United Kingdom around £5.2 billion [2], with the cost to the UK Health Service (NHS) estimated at £342 million at 2009/10 prices [3].

Ongoing, frequent fluctuations in mood (henceforth referred to as *bipolar mood instability* [BPMI]) can occur across days and weeks for some individuals. This pattern is characteristic of cyclothymic disorder, in which individuals experience multiple periods of hypomanic and depressive symptoms with relatively little time free from symptoms, but it is also experienced by individuals with BD I or II outside of acute episodes of mania or depression [4]. Presence of mood instability is a risk factor for future mania or depression, as well as being associated with elevated rates of anxiety disorders, substance use and difficulties in functioning [5–8].

Despite its prognostic importance, there is no gold standard pharmacological strategy for BPMI, and relatively few pharmacological treatment trials focus primarily upon it as a feature of BDs [9, 10]. Established psychological therapies for BD, including cognitive behavioural therapy, focus upon ameliorating depression or preventing major relapse [11], not upon addressing mood instability, which is typically not even measured in trials of these therapies. A small number of published studies have investigated psychological therapies for cyclothymic disorder [12–14] or have considered mood instability within a psychological approach for individuals with BD [15, 16]; however, none have selected those with BPMI across the bipolar spectrum and tested an intervention that directly targets this aspect. Consequently, we sought to develop an intervention that addresses mood instability in all of those with a bipolar spectrum condition who view this part of their condition as a primary problem.

Dialectical behaviour therapy (DBT) [17] was initially developed for individuals with borderline personality disorder, a patient group who also typically experience ‘stable instability’ of mood. Several studies have examined modified versions of DBT as an intervention for full BD, with encouraging results [18–21]; however, these have not specifically selected those with mood instability, nor have they measured this as an outcome. Standard DBT targets key psychological and interpersonal processes hypothesised to contribute to mood instability related to negative emotion (e.g., anger, sadness), but it does not discuss, or equip patients to manage, the hypomanic mood states present in bipolar spectrum conditions. Consequently we adapted standard DBT to take this into account. Our approach (the Therapy for Inter-episode mood Variability in Bipolar [ThrIVe-B] programme) targets not only factors known to precipitate or maintain full bipolar episodes (e.g., routine disruption) [22] but also those likely to exacerbate frequent mood swings (e.g., impulsive responding to minor mood changes, including emerging hypomanic states) [23], as well as some of the consequences of BPMI (e.g., relationship problems, social avoidance and shame) that can act as further sources of stress. Our treatment is informed by our clinical experience with individuals with BPMI, by current theory and evidence regarding basic psychological processes that maintain mood instability, and by input from individuals with lived experience of BD.

In an initial open feasibility study (*n* = 12) we found the ThrIVe-B approach to be acceptable to participants, with 75% of participants who commenced the therapy completing it ([name], [name], [name], [name] & [name]: Psychological Therapy for Mood Instability within Bipolar Spectrum Disorder: Open Feasibility Trial of a Dialectical Behaviour Therapy-Informed Approach, in preparation). The approach was viewed as broadly acceptable by participants, with the majority describing positive changes in symptoms, functioning or well-being which they attributed to the programme. This in conjunction with the pattern of clinical change observed supported further investigation of this approach. To do so, we propose a feasibility trial to resolve uncertainties in trial design and delivery, including the feasibility of running the trial across additional study sites, and to further refine the content and delivery of the intervention. To provide comprehensive information for a future trial, multi-method evaluation is required, including measurements of clinical outcome, cost-effectiveness and process evaluation.

### Objectives

We have the following objectives in this trial:To establish recruitment pathways and trial teams in two trial sitesTo inform the recruitment and timeline of a future fully powered trial by establishing the number of participants initially identified, approached, consented, randomised and completedTo refine future trial procedures by establishing the acceptability and experience of the trial process to participants, including randomisation and completion of outcome measuresTo further assess the acceptability of the treatment via qualitative interviews and, based on input from trial participants and clinicians, to further refine and develop the treatment manual and the procedures for training, supervising and assessing the competence of trial therapistsTo determine the optimal primary outcome measure in a future trial by assessing the performance of selected candidate primary outcome measures with respect to level of acceptability to participants (completion rates, perceived burden) and participant-perceived relevance and valueTo inform estimation of sample size for a future trial by measuring data completeness at follow-up (participant attrition), SD of the likely primary outcome measure, and the variability of the comparator condition, treatment as usual (TAU), across individuals and sitesTo pilot a measure of resource use and to assess the feasibility and acceptability of candidate health economics measures to inform the future definitive trialTo identify, measure and cost the resources needed to deliver the intervention

We will also evaluate whether the following continuation criteria have been met prior to planning a future definitive trial:Trial participation does not lead to serious negative consequences (unexpected serious adverse reaction) for our participants.Any serious concerns about the acceptability and feasibility of the trial procedures can be rectified prior to a full trial.Follow-up data at 9 months are available for at least 60% of participants.At least 60% of patients in the intervention group complete treatment (attend at least 50% of possible sessions).

## Methods/design

This protocol is reported according to the Standard Protocol Items: Recommendations for Interventional Trials (SPIRIT) 2013 statement (*see* Additional file 1 for the completed SPIRIT checklist).

### Design

We will conduct a feasibility study with a two–arm, randomised, parallel, controlled trial design. Participants will be randomised in a 1:1 ratio to TAU only (control arm) or TAU plus the ThrIVe-B programme (intervention arm). Outcome measures will be recorded at baseline and at four follow-up points—3, 6, 9 and 15 months after randomisation—with 9 months as the primary end point and the point of qualitative interview (because all participants will have completed treatment by this point).

### Setting and participants

We will conduct the trial across two sites in the United Kingdom. Participants will be recruited from primary care services, secondary care mental health services and via self-referral. Eligible participants will be aged 18 years or older and have a lifetime diagnosis of BD (I, II, other specified BD) or cyclothymic disorder, according to the *Diagnostic and Statistical Manual of Mental Disorders, Fifth Edition* (DSM-V) [24], criteria. Within this, they must have experienced at least a 2-day period in which symptom criteria for hypomania were met during their lifetime. They must report current BPMI, defined as per DSM-V criteria 1 and 2 for cyclothymic disorder, or by a score of 1.3 on the bipolar subscale of the short form of the Affective Lability Scale (ALS; the mean score on this subscale from previous research with individuals with BD) [6]. They must also be willing to engage in psychological therapy that focusses primarily on ongoing mood instability and its consequences, and they must be willing and able to attend the group therapy sessions as scheduled. Participants must have sufficient competency in English to be able to complete study measures without the need for translation and be registered with a general practitioner (GP) practice in the catchment area served by the NHS trusts involved in the study. They must not have current substance dependence, be receiving other psychological therapy for BD, or lack capacity to consent to treatment or research participation. Participants experiencing an acute manic or depressive episode (according to DSM-V), engaging in frequent, significant self-harming behaviour, at high risk of suicide, or posing a significant risk to other group members will not be eligible for the study. This study locates the ThrIVe-B programme at the interface between primary and secondary care; therefore, participants must not be receiving ongoing co-ordinated care in secondary mental health services.

Neither medication status nor presence of co-morbid psychiatric conditions will serve as exclusion criteria, but this information will be recorded. In neither condition will participants be denied access to routine care, nor will they be excluded from the study if they commence psychological therapy as part of routine care, after the point of randomisation.

### Sample size

A total of 48 participants (24 per group) will allow us to address the stated objectives of this feasibility trial. This represents recruitment to three ThrIVe-B groups at full capacity (8 per group), with equivalent numbers randomised to TAU. On the basis of our previous work on the ThrIVe-B programme, we estimate an attrition rate of 17% with respect to the primary end point at 9 months post-randomisation. Our sample size of 48 will allow us to estimate this level of attrition for a future definitive trial with a precision of ±15% with 95% certainty and allow us to estimate the SDs for any potential primary outcome measures that would inform the power calculation for a definitive trial.

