### Data analysis

#### Quantitative data analysis

Patients’ demographic characteristics at baseline will be reported by treatment group. The primary analyses will be performed after 9-month follow-up and after data cleaning is completed and the database finalised. Further analyses will be performed after the final 15-month follow-up. No interim analyses are planned.

All analyses will be done on an intention-to-treat basis; included outcomes will be reported according to randomised allocation and regardless of the treatment actually received. There will be no possibility of participants allocated to the control arm receiving the intervention; it is possible that participants allocated to the intervention will in actuality receive none of the intervention or will not complete the intervention (defined as attendance of at least 50% of group sessions). All outcomes will be reported descriptively. At 9-month follow-up only, an inferential analysis will be performed for continuous outcomes only, reporting the relevant 95% CI for the between-group mean difference (intervention minus TAU), but no *p* value. Inferential analyses will include the randomisation covariates: site and baseline medication status. No interactions between intervention status and covariates are planned.

Proportions of participants recruited (of those approached) and those lost to follow-up at 3, 6, 9 and 15 months, will be reported with 95% CIs. All analyses will use complete case data only. No attempts to address missing data, such as multiple imputation, will be made.

The economic analysis will take the NHS and social care perspective. No covariate analysis or subanalysis will be conducted, because this is a feasibility trial and is not powered for such inferential analyses. Descriptive data for each arm will be reported with CIs for between-group comparisons. No *p* values will be reported.

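### The ±15% precision quoted for 17% attrition does not follow from 48 participants, who give about ±11 percentage points; the error is conservative and minor

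*Protocol article*

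**What the plan says.** The Sample size section of the protocol article gives every input to the claim.

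- The size: "A total of 48 participants (24 per group"). The section first explains this number by capacity: three therapy groups of eight, with as many again allocated to usual care.
- The expected rate, drawn from the team's previous work on the programme: "we estimate an attrition rate of 17% with respect to the primary end point at 9 months post-randomisation".
- The precision: the sample of 48 is to allow the team to "estimate this level of attrition for a future definitive trial with a precision of ±15% with 95% certainty".

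The same sentence adds that the sample will allow standard deviations of candidate outcomes to be estimated, but attaches no precision to that aim. Under Quantitative data analysis, the proportions of "those lost to follow-up at 3, 6, 9 and 15 months, will be reported with 95% CIs". No split by arm is mentioned there.

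**The concern.** The precision sentence names its sample size (48), its rate (the 17% just introduced) and its confidence level (95%), so it can be checked directly. A half-width of 15 points looks too wide for a proportion near 17% in 48 people.

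What is at stake is limited. The objectives include measuring attrition to help size a definitive trial, and this is the one place where the article says how well 48 participants will do that. A reader who takes the figure at face value gets the wrong expectation of the precision for overall attrition. A reader who recalculates it cannot reconcile the result with the text.

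**Working it through.** **Inputs**, from the Sample size section: N = 48; n = 24 per arm; p = 0.17; two-sided 95% confidence, so z = 1.96; stated half-width 0.15. The 1:1 allocation is confirmed under Design.

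**Formula.** Half-width of a 95% interval for one proportion (Wald): z × √(p(1 − p)/n), with p(1 − p) = 0.17 × 0.83 = 0.1411.

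**Step 1: the plan's figure from its stated inputs.**
1.96 × √(0.1411/48) = 1.96 × 0.0542 = 0.106, or ±10.6 points. The stated ±15% is not reproduced.

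**Step 2: the same inputs with one arm.**
1.96 × √(0.1411/24) = 1.96 × 0.0767 = 0.150, or ±15.0 points. This matches the printed figure.

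**Step 3: solve for n.**
n = 1.96² × 0.1411 / 0.15² = 24.1. At 17%, a half-width of 15 points corresponds to one arm.

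**Step 4: does another method rescue n = 48 at about 17%?**

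| Method | Half-width (points) |
|---|---|
| Wald | 10.6 |
| Wald with continuity correction (adds 1/96) | 11.7 |
| Wilson | 10.5 |
| Clopper–Pearson (7.7% to 30.6%) | 11.4 (upper limb 13.6) |
| Agresti–Coull, 8/48 | 10.7 |
| Jeffreys, 8/48 | 10.4 |

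None reaches 15.

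**Step 5: does another basis rescue it?**

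- Denominator reduced by 17% to 40: ±11.6.
- 99% instead of 95% confidence, n = 48: ±14.0.
- Difference in attrition between arms: 1.96 × √(2 × 0.1411/24) = ±21.3.
- Worst case p = 0.5, n = 48: Wald 1.96 × √(0.25/48) = ±14.1; with continuity correction ±15.2. The largest Clopper–Pearson half-width over all possible counts is 14.8.

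By the Wald formula no rate gives 15 points with 48 people: that needs p(1 − p) = 0.15² × 48 / 1.96² = 0.281, and the maximum is 0.25. The routes at n = 48 and 95% that come near 15 all drop the 17%.

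**The case against.** The best defence is that ±15% is a rounded worst case over all attrition rates with 48 participants, since p = 0.5 gives 14.1 to 15.2 points depending on method. Equally, a true half-width of 10.6 lies inside 15, so the sentence would be harmless if read as a guarantee of no worse than ±15. Neither reading fits the text, which gives a precision for the 17% level and does not call it a bound. What does stand is that the origin of the figure is unproven. The match with n = 24 is close, but a per-arm calculation is an inference.

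Four stronger readings are tempting, and the documents do not support them.

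- *The trial is wrongly sized.* A reader might infer this from a faulty precision statement. The slip runs the other way, since 48 participants do better than claimed. The section also justifies 48 by the capacity of three groups of eight plus equal numbers on usual care.
- *Half the sample would have met the design target.* The article does not present ±15% as a target that set the sample size. It describes what 48 will allow.
- *The error carries into the definitive trial's allowance for dropout.* That allowance would rest on observed attrition, and 95% intervals from the observed data are already planned.
- *Attrition must be reported by arm with a named interval method.* This would be a preference. It does not follow from the arithmetic, and the choice of interval is commonly left to the analysis plan.

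**Conclusion.** The stated precision is wrong as written. For 17% attrition in 48 participants the 95% half-width is about ±11 percentage points (Wald 10.6; 10.4 to 11.7 across the methods tried), not ±15. The printed figure matches one arm of 24 (15.0), but the document does not say that it is per arm.

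The matter is minor. The error is conservative. It alters neither the adequacy of the sample nor the conduct of the trial, and neither 60% continuation criterion (9-month follow-up and treatment completion) uses it. It merits correction because it is the only quantified precision claim for the sample size.

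The conclusion assumes that ±15% means percentage points, that 95% certainty means a two-sided 95% confidence interval, and that attrition is a single proportion of all those randomised. The mismatch itself does not depend on any view of where the 15 came from.

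**What to change.** Correct one sentence in the Sample size section, choosing whichever version reflects what was intended:

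- for overall attrition, say that 48 participants estimate a rate of 17% to within about ±11 percentage points (95% confidence interval); or
- for attrition within arms, keep about ±15 percentage points and say that it applies to each arm of 24.

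The cost is one sentence. Sample size, conduct and planned analyses stay as they are. The Trial status section reports that recruitment ran to July 2018, so the change serves accurate reporting only, and the corrected figure can be carried into the results report.

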### Randomisation, concealment of allocation, and blinding

Eligible participants will be randomised in a 1:1 ratio, with minimisation by trial site and medication status. To ensure concealment, eligible participants will be randomised via a validated password website hosted by the Exeter Clinical Trials Unit. The first ten participants will be allocated using simple randomisation, the remainder being allocated using the minimisation procedure, maintaining a stochastic element to the algorithm to allow concealment to be maintained. Following randomisation of a given participant, he or she will be informed of their allocation by an unblinded member of the research team.

Researchers conducting follow-up assessments will be blind to study arm allocation and will remind participants of the need to conceal their allocation. We will test blindness by asking researchers to indicate at follow-up which treatment they believe the participants received and analyse any correlation with outcome. We will maintain the blinding as far as possible to maintain the quality and legitimacy of the trial and its findings; however, in the unlikely event that a participant has an adverse reaction to either treatment arm, unblinding may occur. We will unblind the researchers only in exceptional circumstances when the knowledge of the treatment arm is deemed essential to the management of the patient by their GP (e.g., serious adverse events). Any unblinding that occurs will be recorded; where possible, researchers who remain blind to participant status will conduct their future follow-up assessments. All statistical analyses will be performed by a statistician using groups indicated by an anonymised code.

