#### Secondary outcome measures

Participants will complete the following measures at baseline and all follow-up points, representing candidate primary outcome measures for a future definitive trial: the Patient Health Questionnaire 9-item scale [27], which measures depressive symptoms; the ALS [28]; the Bipolar Disorder Recovery Questionnaire [29]; and the Quality of Life in Bipolar Disorder scale [30]. Participants will also complete the Generalised Anxiety Disorder 7-item scale [31]. At baseline, 9 and 15 months, the Bech Mania Rating Scale [32], the Hamilton Depression Rating Scale [33] (both observer-rated), and the Brief Adherence Rating Scale for medication adherence [34] will be completed, as will relevant sections of the Structured Clinical Interview for DSM-V [35] to assess both eligibility criteria, and presence of affective episodes during the follow-up period.

In addition, participants will complete the EuroQoL 5-dimension 5-level (EQ-5D-5L) instrument [36] and the 36-item Short Form Health Survey [37] in order to assess how feasible it is to use these measures in this population. This will allow us to identify potential reasons for incomplete data. In the future randomised controlled trial, the scores will be used to obtain utility values for deriving quality-adjusted life-years in order to estimate incremental cost-effectiveness ratio. Participants will be asked also to complete a resource use questionnaire (last 6 months or since last assessment point) to assess the feasibility of collecting health and social service use. Information on the resource use and costs of delivering the ThrIVe-B programme will be collected.

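### The stated test of assessor blinding correlates guesses with outcome; that does not show whether the blind held, and no comparison of guesses with true allocation is stated

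*Protocol article*

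**What the plan says.** The section on randomisation, concealment and blinding states that "Researchers conducting follow-up assessments will be blind to study arm allocation and will remind participants of the need to conceal their allocation". Participants know their arm: after randomisation, each "he or she will be informed of their allocation by an unblinded member of the research team". The check on whether the blind holds is one sentence: "We will test blindness by asking researchers to indicate at follow-up which treatment they believe the participants received and analyse any correlation with outcome". The same section adds that "Any unblinding that occurs will be recorded" and that, where this can be arranged, later assessments pass to a researcher who is still blind.

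The Data analysis section does not mention blinding. No other section states a comparison of guesses with allocation.

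The measures that depend on the assessor are in the Secondary outcome measures section, which names "the Bech Mania Rating Scale [32], the Hamilton Depression Rating Scale [33] (both observer-rated") and parts of the structured diagnostic interview, at baseline, 9 and 15 months. The four candidate primary measures in that section are completed by participants.

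**The concern.** Whether a blind held is a question about guess and allocation: do assessors pick the right arm more often than chance would give? The sentence gives its purpose as testing blindness and its data as the assessor's guess, but the only analysis it names is correlation with outcome. That answers a different question, namely whether belief and ratings move together.

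The two questions can have different answers. Assessors who know nothing may guess from how well someone is doing, and the correlation is then high. Assessors who have been told every allocation produce a correlation only as large as the difference between arms in the ratings, which may be nil.

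At stake is one piece of feasibility information. Participants know their arm and are only reminded to conceal it, so disclosure at interview is an obvious route by which the blind could fail. A definitive trial would want to know how often that happened. The record of unblinding captures known events but not loss of blinding that nobody reports.

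**Working it through.** The protocol attaches no figure to this check, so there is none to reproduce. The steps below ask what the stated correlation would show in known situations.

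**Inputs from the protocol article**
- Sample size section: "A total of 48 participants (24 per group) will allow us to address the stated objectives of this feasibility trial".
- Same section: "we estimate an attrition rate of 17% with respect to the primary end point at 9 months post-randomisation". Hence 48 × 0.83 = 39.8, or about 40 participants at 9 months, 20 per arm.

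**Assumptions (not in the protocol)**
- A normal outcome with SD 1 within each arm, scored so that higher is better.
- A true effect d between 0 and 0.8 SD.
- Assessor bias of 0 or 0.5 SD.
- The guessing behaviours described below.

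**1. Blind intact, guess taken from improvement, d = 0**
- Strict inference: the guess is intervention if the outcome is above the median. The correlation of a median split with its own normal variable is √(2/π) = 0.80.
- Noisy inference: the assessor's impression is the outcome plus independent error of the same SD. The correlation is 0.80/√2 = 0.56.
- In both cases 50% of guesses are correct, which is chance.

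**2. Blind fully broken, guess = allocation**
- With 1:1 allocation, r = d/√(d² + 4).
- d = 0: r = 0.
- d = 0.3: 0.3/√4.09 = 0.15.
- d = 0.5: 0.5/√4.25 = 0.24.
- d = 0.8: 0.8/√4.64 = 0.37.
- In every case 100% of guesses are correct.

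**3. Bias against benefit**
- If there is no true effect but an unblinded assessor shifts ratings by 0.5 SD in favour of the intervention arm, the ratings differ by 0.5 SD between arms and r is again 0.24.
- This is the same value as for a true 0.5 SD effect rated without bias. The correlation cannot tell them apart.

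**4. Scale at this sample size**
- For unrelated variables and n = 40, the sampling SD of r is about 1/√39 = 0.16.
- The value 0.80 from an intact blind lies 0.80/0.16 = 5 SDs from zero. The value 0.24 from a fully broken one lies 0.24/0.16 = 1.5.

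A simulation of 4,000 trials per scenario at n = 40 agrees: mean r was 0.80 and 0.56 in step 1; 0.00, 0.15, 0.25 and 0.37 in step 2; and 0.24 in step 3. Results at n = 48 show the same pattern.

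**5. The alternative, guess against allocation**
- Intact blind at d = 0: 50% correct. Fully broken blind: 100% correct at every d.
- Partly broken, with 80% correct guesses unrelated to improvement: the correlation with allocation is 2 × 0.8 − 1 = 0.60. The correlation with outcome at d = 0.5 is 0.60 × 0.24 = 0.15.
- Limitation: if treatment works, guesses made from improvement alone exceed 50% correct. Under strict inference agreement is Φ(d/2), which is Φ(0.4) = 66% at d = 0.8. With noisy inference the simulation gives 61%.

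**The case against.** The sentence can be read as two steps: guesses are collected to test the blind, and the association with outcome is examined as well. It does not rule out a comparison with allocation, which may have been intended or may sit in an analysis plan that is not shown. How guesses are tabulated is detail that a condensed article may leave out.

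This stands in part. It would be wrong to conclude that the trial team will not make the comparison. But the article is not silent on the analysis. It names one and calls the procedure a test of blindness, and elsewhere it uses outcome to mean measured endpoints. The named analysis does not do what it is said to do, whatever else may be planned.

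The illustrations rest on stylised behaviour, and this stands too. The 0.80 follows by construction from a median split and says nothing about these particular assessors. The zero under a broken blind needs both no effect and no rating bias, in which case the ratings are not distorted. The protocol also sets no significance threshold for the check, so rates of significant results would not describe how it will be used and are not relied on here.

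A reader might infer that the check could reverse a decision about the definitive trial. The documents do not support that: none of the four continuation criteria concerns blinding. Nor do they support an inference that the main comparisons are compromised, since the candidate primary measures are completed by participants who already know their arm. Finally, the guess-outcome association has a proper secondary use, as a look at whether belief tracks ratings.

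**Conclusion.** The point holds, with limited reach. The article presents a guess-outcome correlation as the test of blindness and states no comparison with true allocation. That correlation can be high with an intact blind, can be near zero with a fully broken one, and cannot separate assessor bias from true benefit. The figures show that these things can happen under the assumed behaviour; they do not predict what this trial will find.

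What is affected is the trial's evidence on whether assessors can be kept blind for the two observer-rated scales and the diagnostic interview. Guesses and allocations are both held, so nothing is lost irrecoverably. The correction is still worth making, because it is nearly free and supplies information that a feasibility trial is well placed to collect.

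**What to change.** State that assessor blinding will be assessed by cross-tabulating the guess against true allocation, by arm, at the 9- and 15-month interviews, with the proportion correct and its 95% CI. A blinding index is optional. Keep the guess-outcome association as a separate descriptive analysis and do not call it the test of blindness.

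Preferably, record why the assessor made each guess (disclosure by the participant, or perceived improvement), because an effective treatment can by itself raise agreement above 50%.

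The cost is one sentence in the analysis text and one extra form item, with no more participants. Two practical limits remain. Precision is modest: at 50% correct, the half-width of the 95% CI is about 1.96 × √(0.25/20) = 22 percentage points per arm and 1.96 × √(0.25/40) = 15 points overall, so the result should be read as descriptive. And because the statistician works with coded groups, counting correct guesses requires the code to be revealed, so this table is best produced after the outcome analyses.
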